#### 2.8.2. Analysis methods

The major analysis will be based on the results of the assessment of 4 weeks after treatment. FMA-UE score, SEP-related index, UEFT score, WMFT score, reNSA score, MBI score, and DTI-related data are all measurement data. For within-group comparisons, if the data conformed to normal distribution, paired *t*-test will be used to compare SEP and DTI results, and other data will be performed using repeated measures ANOVA, and least significant different (LSD) methods will be used for pair comparison; for data that do not fit the normal distribution, the Wilcoxon rank-sum test will be used for SEP and DTI results, and the Generalized estimating equation (GEE) approach will be used for all other data. Between-group comparisons will be performed by analysis of variance with a factorial design, and interaction effects and main effects will be analyzed. In addition, Pearson correlation analysis or Spearman's analysis will be used to analyze the correlation among indicators. For the incidence of adverse events among groups, Fisher's exact test will be used. Statistical treatments were all performed using a two-sided test with an inspection level of α = 0.05.

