**Methods:**

This is a single-center, randomized controlled trial using a 2 × 2 factorial design. We will recruit 136 stroke survivors with upper extremity dysfunction and randomize them into four groups (*n* = 34). All subjects will undergo routine treatment, based on which the Experimental Group 1: rehabilitation training synchronized with intradermal acupuncture treatment of the affected upper limb; Experimental Group 2: rehabilitation training of the affected upper limb synchronized with focal-side scalp acupuncture treatment, and Experimental Group 3: rehabilitation training synchronized with intradermal acupuncture treatment of the affected upper limb synchronized with focal-side scalp acupuncture treatment; Control Group: rehabilitation training of the affected upper limb only. The intervention will last for 4 weeks, 5 times a week. Both acupuncture treatments will be performed according to the Revised Standards for Reporting Interventions in Clinical Trials of Acupuncture (STRICTA). The primary outcome indicators for this trial are Fugl-Meyer Assessment-Upper Extremity and Somatosensory Evoked Potential. Secondary outcome indicators include Wolf Motor Function Test, Upper Extremity Function Test, revised Nottingham Sensory Assessment Scale, Diffusion Tensor Imaging, and Modified Barthel Index. The incidence of adverse events will be used as the indicator of safety.

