### 2.4. Sample size

This study is a RCT with a 2×2 factorial design in which the FMA-UE scores of stroke patients were used as the primary outcome indicators. Based on the results of the preliminary pre-experiment and combined with the relevant literature (24), we used PASS15.0 software (PASS, Kaysville, UT, USA) for sample size estimation. Based on previous studies, we were informed that the mean values of FMA-UE scores after treatment for the four groups were 41.36, 48.21, 52.87, and 40.54, respectively. After calculation, the standard deviation of the two-factor interaction was 0.96, and the estimate of the overall standard deviation was 3.38. The test level was set at α = 0.05 (bilateral test) with a certainty of 1-β = 0.9. The sample size required was 34 cases in each group, and a total of at least 136 patients needed to be included, according to 1:1:1:1 parallel grouping, taking into account the 10% dropout rate of the study population.

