SEP is the potential induced in different parts of the central nervous conduction pathway after the skin or peripheral nerve receives certain pulse electrical stimulation. It has the advantages of high sensitivity, strong specificity, and repeatability (28). As an objective test, it excludes the influence of patient's subjective factors, which makes the evaluation results more reliable; SEP not only provides an objective assessment of stroke limb sensory function and feedback on the therapeutic effect of limb rehabilitation, but also guides the formulation of limb rehabilitation protocols and clinical treatment, and is considered an important reference indicator for predicting the prognosis of stroke limb function (29, 30). The main observations of SEP are latency and wave amplitude, with latency related to the brain white matter and wave amplitude related to axons and cortex. N20 arises in the primary somatosensory cortex and is the first near-field potential of SEP (31). In this study, an EMG-evoked potential device (Dantec, Denmark) will be used for median nerve SEP testing. A saddle stimulating electrode will be placed 2–3 cm above the transverse carpal tunnel of the upper limb on the hemiplegic side of the patient. According to the 10–20 international system of EEG electrode placement (32), the recording electrodes were located at C3' & C4' of the head contralateral to the limb under test, and the reference electrode is placed at Fz. The electrode impedance will be kept below 5 kΩ. Constant current square wave pulses will be used with a frequency set at 5 Hz and a pulse width of 0.2 ms, with a stimulation intensity sufficient to elicit slight thumb movement. Two median nerve N20 SEP examinations will be performed for each evaluation, each time superimposed 200 times, and the latency and wave amplitude of the N20 wave will be recorded, and the average value of the two times will be taken as the final test result.

Assessment time points: baseline, and 4 weeks after treatment.

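### The within-group fallback for non-normal SEP and DTI names an unpaired test (Wilcoxon rank-sum) for paired before-after data; a minor correction that does not affect the randomized comparison

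*Protocol article*

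**What the plan says.** Section 2.8.2 of the protocol article sets the within-group methods first. For normal data: "For within-group comparisons, if the data conformed to normal distribution, paired *t*-test will be used to compare SEP and DTI results". For data that do not fit the normal distribution: "the Wilcoxon rank-sum test will be used for SEP and DTI results". The outcomes with more than two assessments go to repeated measures ANOVA or to GEE.

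Section 2.6.1 gives the SEP schedule: "Assessment time points: baseline, and 4 weeks after treatment". Section 2.6.2 gives the same two times for DTI, and Table 1 agrees. SEP is one of the two primary outcomes; DTI is secondary.

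The comparison between treatments has its own sentence in section 2.8.2: "Between-group comparisons will be performed by analysis of variance with a factorial design, and interaction effects and main effects will be analyzed". All tests are at two-sided 0.05.

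**The concern.** A within-group SEP or DTI comparison sets each patient's 4-week value against the same patient's baseline. The plan recognises the pairing when the data are normal and drops it when they are not. The rank test that corresponds to the paired t-test is the Wilcoxon signed-rank test. The rank-sum test treats the two sets of values as if they came from different people.

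Applied as written, the p-values would not have their stated level and some within-group change could be missed. A Shapiro-Wilk result would also decide whether pairing is used. SEP change in one arm could then be tested as paired and in another as unpaired, so that the two p-values would not be comparable.

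**Working it through.** **Which comparison the test serves.** The clause sits in the within-group sentence, opposite a paired t-test. There are only two measurement times, so each patient gives one pair. It cannot be a between-group test, because the next sentence assigns those comparisons to factorial ANOVA, and a two-sample test would not suit four arms. No reading makes an independent-samples test the right one here.

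**Inputs from the article.** Two-sided alpha 0.05 (section 2.8.2); 34 patients per arm (section 2.4). A 10% dropout would leave about 31 (34 × 0.9 = 30.6).

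**Inputs not in the article, so assumed.** The baseline-to-4-week correlation (rho), taken over 0 to 0.9, and the size of the change, taken as 0.3 to 0.8 SD. The article states no figure for these tests, so there is none to reproduce.

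**Type I error by formula.** For bivariate normal pairs in large samples, the true null variance of the rank-sum statistic is the assumed variance multiplied by 1 − (6/π)·arcsin(rho/2). The actual two-sided error is therefore

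2 × [1 − Φ(1.96 / √(1 − (6/π)·arcsin(rho/2)))]

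- rho 0.5: factor 1 − 1.910 × 0.2527 = 0.517; 1.96/√0.517 = 2.72; error 0.0064.
- rho 0.7: factor 1 − 1.910 × 0.3576 = 0.317; 1.96/√0.317 = 3.48; error 0.0005.

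**Type I error by simulation** (10,000 runs per setting, n = 34, bivariate normal):

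| rho | rank-sum |
|---|---|
| 0 | 5.3% |
| 0.3 | 2.1% |
| 0.5 | 0.8% (0.7% in a repeat run) |
| 0.7 | 0.1% |
| 0.8 and above | below 0.1% |

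The signed-rank test stayed between 4.4% and 5.2% at every rho. Lognormal data matter here because the branch applies to non-normal data; they gave rank-sum error of 2.0%, 0.75% and 0.11% at rho 0.3, 0.5 and 0.7. With n = 31 the pattern is the same.

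**Power, rank-sum against signed-rank** (n = 34, normal data):

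| Shift | rho 0 | rho 0.5 | rho 0.7 | rho 0.9 |
|---|---|---|---|---|
| 0.3 SD | not run | 15 / 38% | 10 / 57% | not run |
| 0.4 SD | 36 / 34% | 31 / 60% | 27 / 81% | 21 / 100% |
| 0.5 SD | 51 / 50% | 51 / 79% | 53 / 95% | 57 / 100% |
| 0.8 SD | not run | 95 / 99% | 98 / about 100% | about 100 / 100% |

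Share of power lost at 0.4 SD: (60 − 31)/60 = 48% at rho 0.5, (81 − 27)/81 = 67% at 0.7, and (100 − 21)/100 = 79% at 0.9. At 0.5 SD: (79 − 51)/79 = 35%, (95 − 53)/95 = 44%, and (100 − 57)/100 = 43%. At 0.8 SD the loss is about 4 points at most. Lognormal data at 0.5 SD and rho 0.5 give 52% against 75%, so the pattern does not rest on normality.

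**The case against.** The strongest defence is that this is a naming slip. The sentence is about within-group comparisons and sets the test beside a paired t-test, so a careful analyst would see that a paired test was meant. That is probably right, and it bears on how serious the point is. It does not remove the point: the article names a specific test, nothing elsewhere in it corrects the name, and an analyst would have to run the wrong test or depart from the published plan.

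Three stronger readings are tempting, and the article does not support them.

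- A reader might infer that the primary SEP efficacy test is broken, because SEP is a primary outcome. It is not. Treatment effects and the interaction are tested by factorial ANOVA, which this clause does not touch. An uncontrolled before-after change within one arm carries no treatment claim.
- A reader might take p-values at the wrong level to mean false positive findings. Under positive within-patient correlation, the natural expectation for repeated measurements, the error runs the other way: the test rejects too rarely.
- A reader might conclude that most of the power is lost and that real change would usually be missed. That holds for small shifts with high correlation. It fails at correlation 0 and at 0.8 SD, and at 0.5 SD less than half the power is lost. The article gives neither the correlation nor the effect size needed to choose among these cases.

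The branch is also conditional: it applies only if SEP or DTI values are judged non-normal, and the article does not say how likely that is.

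**Conclusion.** The clause is wrong as written. It names an independent-samples test for paired data and contradicts the paired t-test that the plan gives for the same comparison. That conclusion follows from the text and needs no assumption.

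The size of the effect does rest on assumptions. With positive correlation the test is conservative, far below its nominal 5% once the correlation reaches 0.5. The power cost runs from nothing to most of the power, depending on two quantities the article does not state. Because the harm is confined to a conditional, within-group, secondary use of the data and leaves the randomized comparison intact, this is a minor correction.

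**What to change.** In section 2.8.2, for the within-group SEP and DTI comparisons, replace Wilcoxon rank-sum test with Wilcoxon signed-rank test. Nothing else in the sentence needs to change. The signed-rank test holds its level at every correlation examined and matches the paired t-test in the normal branch.

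The cost is one word: no extra patients, assessments or data. Section 2.10 already provides the route, a revision submitted to the ethics committee and then recorded at the registry. If a separate analysis plan exists, its wording should be checked for the same term.

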### 2.3. Randomization, allocation concealment, and blinding

In this study, a stratified blocked randomization method will be used to stratify patients by age (18–45 years old, 46–75 years old) and type of stroke (cerebral hemorrhage, cerebral ischemia), and SPSS 26.0 software (IBM, Armonk, NY, USA) will be used to stratify and randomize 136 patients who met the criteria for upper limb dysfunction after stroke. The patients will be randomly divided into EG1, EG2, EG3, and CG in a ratio of 1:1:1:1, with 34 patients in each group. The personnel responsible for randomization will not be involved in the process of patient recruitment, treatment, assessment, data collection, and statistical analysis. The grouping results will be placed in sealed, opaque envelopes. Subjects will be numbered according to the time of enrollment, and the appropriate envelopes will be given to the person performing the study intervention according to the number.

To exclude as much bias as possible, the assessors and statistical analysts will be blinded, with 2 assessors who are professionally and uniformly trained and 2 other staff members who are responsible for entering and analyzing the data, regardless of patient assignment and without contact with treatment staff.

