### 2.6. Outcome measures

#### 2.6.1. Primary outcome measures

(1) *FMA-UE* will be used to evaluate the patients' upper limb movement function.

This scale is one of the most widely used clinical scales for assessing upper extremity motor recovery after stroke, with 33 items, divided into 3 levels of scores, 0, 1, and 2 points respectively, according to the degree of task completion, and the total score was 66, with higher patient scores suggesting better motor function. FMA-UE is quantified by indicators and has the advantages of being detailed, reliable, and sensitive, which has been established as a standardized assessment tool to measure upper limb movement function (27).

Assessment time points: baseline, and 2 weeks, 4 weeks, 3 months, and 6 months after treatment.

(2) *SEP* will be used to assess the sensory function.

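### The 4-week factorial ANOVA leaves out the baseline value and the randomisation strata, giving up precision that a factorial ANCOVA would recover at almost no cost

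*Protocol article*

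**What the plan says.** Section 2.8.2 bases the main analysis on the 4-week assessment and gives the between-group model as follows: "Between-group comparisons will be performed by analysis of variance with a factorial design", with interaction and main effects to be examined. No covariate is named. Repeated measures ANOVA and GEE also appear in that section, but for within-group comparisons only.

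The information needed for adjustment is already in the design:

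- **Baseline.** For FMA-UE, section 2.6.1 gives "Assessment time points: baseline, and 2 weeks, 4 weeks, 3 months, and 6 months after treatment". SEP is measured at baseline and 4 weeks. Table 1 shows a baseline assessment for every efficacy outcome.
- **Strata.** Section 2.3 says that "a stratified blocked randomization method will be used to stratify patients by age (18–45 years old, 46–75 years old) and type of stroke", with stroke type in two levels.

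Section 2.4 plans the sample size on post-treatment scores: "the mean values of FMA-UE scores after treatment for the four groups were 41.36, 48.21, 52.87, and 40.54, respectively". It adds that "the standard deviation of the two-factor interaction was 0.96, and the estimate of the overall standard deviation was 3.38".

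**The concern.** Eligibility (section 2.2.1) runs from Brunnstrom stage II to IV and from 2 weeks to 6 months after onset. Starting FMA-UE is therefore likely to differ widely between patients, and severity is not a stratification factor. A baseline score that predicts the 4-week score accounts for part of the residual variance. A model without it leaves that part in the error term.

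Stratifying by age and stroke type balances those factors across groups. If they predict outcome, the true sampling variance of the contrasts falls, but a model without them does not register the fall. Its standard errors are then too large and the test is conservative.

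Most is at stake for the interaction, which carries the synergy question named as an aim in the abstract and the Discussion. In a balanced 2 × 2 layout, omitting baseline inflates the variance of all three contrasts by the same proportion. The interaction has the least power to spare because its planned effect is the smallest.

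**Working it through.** **Inputs from section 2.4.** The four post-treatment means, read in the order EG1, EG2, EG3, CG: 41.36, 48.21, 52.87, 40.54. SD of the interaction effects 0.96; overall SD 3.38. "The test level was set at α = 0.05 (bilateral test) with a certainty of 1-β = 0.9". Allocation 1:1:1:1. Size: "The sample size required was 34 cases in each group, and a total of at least 136 patients needed to be included", said to allow for 10% dropout.

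**Input not in the documents.** The correlation r between the baseline and 4-week score. I take 0.3 to 0.8 as an assumed range.

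**Step 1: reproduce the effect size.** Interaction contrast = (52.87 − 48.21) − (41.36 − 40.54) = 4.66 − 0.82 = 3.84. Each cell's interaction effect is ±3.84/4 = ±0.96, which matches the plan and supports the assumed group order.

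**Step 2: reproduce the sample size.** For the one-degree-of-freedom interaction F test in an unadjusted 2 × 2 ANOVA, λ = N × (0.96/3.38)² = N × 0.08067, with N − 4 error degrees of freedom and α = 0.05.

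| Evaluable N | λ | Power |
|---|---|---|
| 132 (33 per group) | 10.65 | 89.95% |
| 136 (34 per group) | 10.97 | 90.8% |
| 122 (136 × 0.9 = 122.4) | 9.84 | 87.5% |

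So 34 per group is the smallest number that meets the 90% target with this unadjusted test, before any dropout. Allowing for 10% dropout gives 34/0.9 = 37.8, that is 38 per group and 152 in total.

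**Step 3: main effects.** Scalp: [(48.21 + 52.87) − (41.36 + 40.54)]/2 = 9.59. Intradermal: [(41.36 + 52.87) − (48.21 + 40.54)]/2 = 2.74. Unadjusted power exceeds 99% for both, with or without the dropout. The interaction is the only one of the three tests near its limit.

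**Step 4: adjust for baseline.** Taking 3.38 as the SD of the raw post-treatment score, residual SD = 3.38 × √(1 − r²). With N = 122, λ = 9.84/(1 − r²). Three further degrees of freedom are charged (baseline, age stratum, stroke type), leaving 115 for error.

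| Assumed r | Residual SD | λ | Interaction power, N = 122 |
|---|---|---|---|
| none (unadjusted) | 3.38 | 9.84 | 87.5% |
| 0.3 | 3.224 | 10.8 | 90.3% |
| 0.5 | 2.927 | 13.1 | 94.9% |
| 0.7 | 2.414 | 19.3 | 99.2% |
| 0.8 | 2.028 | 27.3 | 99.9% |

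The gain shown comes from baseline alone. The strata are charged for but credited with nothing, because the documents do not show how strongly age group or stroke type predicts FMA-UE.

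**The case against.** **The sample size does not rely on adjustment.** A reader might infer that the plan forgoes power its sample size depends on. The documents do not support that: step 2 shows that 34 per group is exactly what the unadjusted test needs, so planning and analysis agree. The fall to 87.5% arises because 136 holds no real dropout allowance, although section 2.4 says it does. That is a separate error, which adjustment would offset but did not cause.

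**The contrast is not biased.** A reader might also infer that chance baseline imbalance invalidates the comparison. It does not. Under randomisation the unadjusted contrast is unbiased and its standard error already reflects such imbalance. Leaving out the strata makes the test conservative at worst and does not raise the false-positive rate.

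**The article may be silent rather than wrong.** It is condensed, a covariate list is often left to an analysis plan, and section 2.8.2 does not say whether scores or changes are analysed. This stands in part: covariates are not expressly excluded, and raw scores are only the natural reading given the post-treatment means in section 2.4. But the article does name its between-group model, and as named the model has no baseline or stratum term.

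**The size of the gain is assumed.** This stands. No correlation is given, and section 2.4 does not say what kind of SD 3.38 is. If it is already a change-score or residual SD, step 4 counts some of the gain twice.

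**Conclusion.** The point holds as one of efficiency, not validity. The named between-group model uses neither a baseline that is measured for every efficacy outcome nor the two factors on which randomisation is stratified.

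The unadjusted figures (90.8% and 87.5%) rest only on the plan's own inputs and its stated dropout. The adjusted figures rest on two assumptions: the correlation, and the reading of 3.38 as a raw-score SD. Under these, a correlation of about 0.3 is enough to bring interaction power back to 90% at 122 evaluable. The benefit from the strata is directionally clear if they are prognostic, but cannot be sized from the documents. The change should be made; the trial is not unsound without it.

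**What to change.** Replace the ANOVA sentence in section 2.8.2 with a factorial ANCOVA, prespecified before unblinding:

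4-week value = scalp + intradermal + scalp × intradermal + baseline value of that outcome + age stratum + stroke type.

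Apply it to FMA-UE and to the SEP measures, and likewise to the other continuous outcomes. Leave the dropout allowance in section 2.4 to be corrected on its own account.

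The cost is one sentence of wording and three error degrees of freedom (118 to 115 at 122 evaluable). All covariates are already collected, and recruitment and conduct are unaffected.

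### Two primary outcomes (three variables) and three factorial effects are each tested at 0.05, the sample size covers only the FMA-UE interaction, and no rule says which test decides the trial

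*Protocol article*

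**What the plan says.** The abstract gives two primary outcomes: "The primary outcome indicators for this trial are Fugl-Meyer Assessment-Upper Extremity and Somatosensory Evoked Potential". Section 2.6.1 lists the same two, FMA-UE for motor function and SEP for sensory function. It describes SEP through two measurements, "The main observations of SEP are latency and wave amplitude", and says that "the latency and wave amplitude of the N20 wave will be recorded". Neither is singled out as the primary SEP variable.

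Section 2.4 sizes the trial on one outcome, describing a 2 × 2 factorial design "in which the FMA-UE scores of stroke patients were used as the primary outcome indicators". Its inputs are the two-factor interaction and a residual standard deviation, both for FMA-UE. SEP does not appear there.

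Section 2.8.2 takes the 4-week assessment as the major analysis. Between-group comparison is by factorial analysis of variance, with both main effects and the interaction examined. One significance level covers everything: "Statistical treatments were all performed using a two-sided test with an inspection level of α = 0.05".

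**The concern.** The design is built around one test, while the analysis section permits nine on primary variables: three variables (FMA-UE, N20 latency, N20 amplitude) times three effects (scalp, intradermal, interaction). All are at 0.05. There is no testing order, no division of alpha, and no statement of whether one or all primary outcomes must succeed.

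Two things are at stake. First, the 5% error level need not hold for the trial's primary conclusion. A significant effect on N20 latency alone could be presented as a primary success while the FMA-UE interaction, the one test that was powered, fails. Second, SEP has primary status with no stated effect size, variability or power, so a null SEP result could not be interpreted as evidence of no effect.

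The trial aims to determine whether the two needling techniques act synergistically. A decision rule chosen after the data are seen could not protect that conclusion.

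**Working it through.** **Step 1. Reproduce the sample size.** Section 2.4 says that "the mean values of FMA-UE scores after treatment for the four groups were 41.36, 48.21, 52.87, and 40.54, respectively". I read these in the protocol's group order: EG1 (intradermal), EG2 (scalp), EG3 (both), CG (neither).

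- Interaction contrast: 52.87 − 48.21 − 41.36 + 40.54 = 3.84.
- Standard deviation of the interaction effect: 3.84 / 4 = 0.96.

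This matches the stated inputs, "the standard deviation of the two-factor interaction was 0.96, and the estimate of the overall standard deviation was 3.38", and so supports the assumed group order. The effect size is f = 0.96 / 3.38 = 0.284.

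Power comes from the noncentral F distribution with 1 and 4n − 4 degrees of freedom and noncentrality 4n × 0.284²:

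| n per group | Power at two-sided 0.05 |
|---|---|
| 33 | 0.8995 |
| 34 | 0.908 |

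The first n to reach 0.90 is 34. The stated 34 per group is therefore the number for exactly one test, the FMA-UE interaction at an unadjusted 0.05.

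**Step 2. Error rate by decision rule.** For k independent tests at 0.05 with every null hypothesis true, the chance of at least one significant result is 1 − 0.95^k.

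- Interaction only, three variables: 1 − 0.95³ = 14.3%.
- All effects, FMA-UE plus one SEP variable: 1 − 0.95⁶ = 26.5%.
- All effects, three variables: 1 − 0.95⁹ = 37.0%.

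The outcomes may be correlated, and the documents give no value. A simulation of the 2 × 2 analysis (34 per group, 40,000 runs, all effects null, equal correlation r among the three variables) gave:

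| r | Any of three interactions | Any of nine tests |
|---|---|---|
| 0 | 14.2% | 36.5% |
| 0.3 | 13.7% | 35.3% |
| 0.5 | 12.6% | 33.2% |
| 0.7 | 11.1% | 29.2% |
| 0.9 | 8.3% | 22.9% |

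If all primary tests had to be significant, the chance of a false overall success could not exceed 5%.

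**Step 3. Power for the FMA-UE interaction if alpha is shared.** With the interaction as the only effect tested and Holm across three variables, the first step uses 0.05 / 3 = 0.0167. The method is that of Step 1. Ten percent dropout from 34 leaves 34 × 0.9 = 30.6, so 30-31 per group.

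| Evaluable per group | Power at 0.05 | Power at 0.0167 |
|---|---|---|
| 34 | 91% | 81% |
| 31 | 88% | 77% |
| 30 | 87% | 75% |

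**The case against.** **The nine-test figure.** A reader might infer that the trial has about a 29-37% chance of a false primary claim. The documents do not support that as a statement of fact. It needs all nine effects to be null, a success rule of any one in nine that the protocol never states, and an outcome correlation between 0 and 0.7. It also pools factorial effects that many statisticians would leave unadjusted, because the scalp, intradermal and synergy effects answer separate questions. FMA-UE and SEP are also assigned to different domains. This objection stands, so the nine-test figure is only an upper scenario.

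**Whether section 2.4 contradicts 2.6.1.** Section 2.4 says that "the FMA-UE scores of stroke patients were used as the primary outcome indicators"; it does not say that FMA-UE is the only primary outcome. Sizing on one of two primaries is not in itself a contradiction. This also stands: the defect is that SEP is primary without power and no decision rule links the two.

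**The unseen analysis plan.** Multiplicity rules are often left to the statistical analysis plan, and a nominal 0.05 in an article does not exclude one. This stands only in part. The protocol is not silent: it sets 0.05 for every test and gives two outcomes primary status. A later rule would have to override that text.

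**Visits.** Multiplicity over time points is already limited, since 4 weeks is fixed as the major analysis. I accept this and count no visits.

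**Conclusion.** The point holds. The protocol gives primary status to two outcomes comprising three variables, tests three effects on each at an unadjusted 0.05, powers one of those tests, and gives no rule for the primary conclusion.

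The size depends on the missing rule. For the synergy question, which is what the trial was sized for, the false-positive chance is about 8-14% if any of the three variables may carry the claim. The most permissive any-of-nine reading gives about 23-37%. Both ranges assume that every effect concerned is null and that outcome correlation runs from 0.9 (lower end) to 0 (upper end). A rule requiring all to succeed would cause no inflation, but none is stated. The lack of any power statement for SEP does not depend on these assumptions.

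**What to change.** In sections 2.6.1 and 2.8.2, name the scalp by intradermal interaction on FMA-UE at the 4-week assessment as the single primary test, at two-sided 0.05. This matches section 2.4 and needs no alpha adjustment. Make N20 latency and N20 amplitude key secondary outcomes, and align the abstract.

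Report the two FMA-UE main effects as separately stated secondary questions, not gated on the interaction. With the planning means, the scalp main effect is (48.21 + 52.87)/2 − (41.36 + 40.54)/2 = 9.59 points, against an interaction contrast of 3.84. Gating would place the largest expected effect behind a smaller one, and two treatments that work additively would yield no claim. Make no confirmatory claim from SEP or the remaining outcomes.

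If SEP must stay primary, state that the interaction is the tested effect and apply Holm across the three variables, so that the family is three tests. Holm across variables without naming the effect would leave three effects per variable uncontrolled. Then restate the FMA-UE interaction power at the first Holm step: about 81% with 34 evaluable per group, and about 75-77% with 30-31 after 10% dropout.

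**Cost.** SEP loses co-primary status or, under Holm, the stated power falls. Section 4 gives January 1, 2023 as the start of recruitment, so under section 2.10 the change needs ethics approval and a registry revision. It should be made before outcome data by group are seen. No new data or patients are needed if the lower power under Holm is accepted.
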